**Methods:**

The platform will include a server that centralizes all the data and business rules, a website dashboard for health professionals, and a mobile app for patients. We will analyze the effects of its use through a controlled, nonrandomized, nonblind, prospective, monocentric clinical trial. We will enroll 68 participants diagnosed with arterial hypertension and under medical follow-up and categorize them into two groups. The participants of the intervention group will use the platform as a monitoring method, whereas the participants of the control group will use conventional methods. In both groups, we will assess and compare the evolution of blood pressure and treatment adherence before, during, and after the intervention.

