#### Study Population and Sample

The study population will include men and women under treatment for arterial hypertension who will be assisted by health professionals in the public health system of a Brazilian city. After the invitation to take part in the study, the participants will sign a consent form. The effect (primary outcome) is expected to be 80% in the intervention group and 40% in the control group, which means a 40% difference. These proportions are based on the findings of the study by Neumann et al [22], which was conducted with a similar design, and also on more optimistic results obtained from one of our pilots [19]. For sample calculation, we used Epi Info version 6.0 software (Centers for Disease Control and Prevention, Atlanta, Georgia; sample size/2 proportions). We considered an estimate of 40% proportion difference between groups, 95% confidence interval, and 80% statistical power (beta). The calculation resulted in 28 individuals for each group, but to minimize the effects of loss and refusal during the intervention, we added 20% to the size, yielding a total of 34 individuals in each group.

The allocation of patients in each group will be based on the eligibility criteria. For example, if the patient fits all the criteria but does not have a mobile phone compatible with the app, then he or she will be allocated to the control group. If the patient has a mobile phone compatible with the app, he or she will be allocated to the intervention group. For propensity score calculation, based on the effect of confounding factors or predictors of exposure (to intervention), we will consider demographic variables of age, gender, and socioeconomic status.

We will consider the following inclusion criteria:

Cognitive ability confirmed by the Mini-Mental State Examination [23] (both groups)Current medical monitoring for the treatment of hypertension in the public health system of the city of Passo Fundo, RS, Brazil (both groups)Possibility to measure blood pressure in drugstores, hospitals, Family Health Strategies, or centers for comprehensive health care (both groups)Possession of an Android mobile phone, version 4.3 or higher (intervention group)Familiarity with the use of apps (intervention group)Internet access on the smartphone (intervention group).

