#### Evaluation and Assessment Frameworks

We will use the following assessment instruments:

Mini-Mental State Examination: It verifies the integrity of cognitive functions, assessing the functions of space-time orientation, memory, attention, calculus, language, and constructive praxis. It includes 11 tasks, with a score ranging from 0 to 30 points. Brucki et al [23] adapted it to the Brazilian context. The cut-off points relate to the years of schooling of the subjects, ie, for illiterate individuals, 19 points; 1-3 years of schooling, 23 points; 4-7 years of schooling, 24 points; and more than 7 years of schooling, 28 points.Sample characterization and sociodemographic questionnaire: It includes questions on age, level of education, income, and experience in using a blood pressure meter. The project researchers will provide the specifications.Martín-Bayarre-Grau questionnaire (MBG): It assesses the therapeutic adherence for arterial hypertension. Alfonso et al [24] developed and validated this instrument, and Matta et al [25] adapted it to the Brazilian Portuguese language.Dietary intake questionnaire by the Brazilian Food and Nutrition Surveillance System (SISVAN): from the Brazilian Ministry of Health [26], this questionnaire identifies the intake frequency of some foods and beverages over the last 7 days through 10 questions. Each item may relate to healthy food or nonrecommended unhealthy food.Engagement questionnaire: It assesses the attributes of engagement, such as esthetics, sensory appeal, concentration, awareness, challenge, control, feedback, interest, motivation, novelty, and time perception. O’Brien and Toms [27] proposed and validated the model, and Cechetti et al [17] translated it to Portuguese.Acceptance questionnaire: This is based on the technology acceptance model (TAM) [28]. The assessment relies on three categories: perceived utility (determines the degree to which a person believes the use of a technology may improve performance and productivity), ease of use (determines the degree to which a person believes the use of a system will be easy to learn and interact with), and external variables (provide understanding about what influences perceived utility and ease of use).Usability assessment questionnaire: This is in accordance with the System Usability Scale (SUS), related to the ease of use and use effort. Brooke [29] developed this framework.Comfort assessment questionnaire for the wearable device: It aims to verify the comfort and well-being of users while trying the wearable technology. The project researchers will produce this instrument.Characteristics of app use: It considers the number of accesses, number of records per period, response to notifications, and reminders. The system usage logs will calculate all this information. We will also use open questions so that participants can report their experience.Health professional assessment: We will perform a semistructured interview with health professionals to verify opinions on the characteristics and resources of the eHealth platform. Questions include, but are not limited to the following: (1) As a health professional, do you believe that the app and dashboard’s features can facilitate the clinical practice to monitor a patient? In what way? (2) Do you believe that a patient can benefit from the app’s features in his or her treatment? In what way? (3) What changes do you suggest for this platform to make it more useful or applicable to clinical practice?

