#### Preintervention Period

After verifying the inclusion criteria, all participants will have a 1-hour meeting with the researchers for instructions on the objective of the study and for signing a consent form detailing all the study procedures. We will register the participants of the intervention group in the system and instruct them about the app’s use. We will collect the preintervention data from both groups from a sample characterization questionnaire and an MBG questionnaire [24].

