#### Statistical and Qualitative Analysis

Our expectation for the primary outcome is the reduction and stabilization of blood pressure. For the secondary outcome, we hope for acceptance of the eHealth platform and improvements in treatment adherence, physical activities, and dietary intake. A priori levels will be set according to the assessment tool and the expected outcome. The acceptance of the eHealth platform will consider good scores obtained in the analysis of usage logs and questionnaires of engagement, SUS, and TAM. Improved adherence to treatment will consider MBG questionnaire scores measured before and after the intervention. For the analysis of physical activities and dietary intake, a binary outcome will consider whether the patient has adequate levels, diagnosed according to the SISVAN’s questionnaire and standards.

For qualitative data, we will use Minayo’s guidelines [30]. Numeric data will be analyzed with statistical software SPSS 22 (IBM Corp, Armonk, New York). We will calculate the measures of central tendency and dispersion of the quantitative variables, and we will use the Kolmogorov-Smirnov test to verify normality. Basic quantitative data will be determined by mean, standard deviation, and median. Categorical data will be determined by simple frequency. Blood pressure data will be analyzed with the paired *t* test. Either the paired *t* test (parametric) or the Wilcoxon test (nonparametric) may be applied to compare other quantitative variables before and after the intervention. To assess treatment adherence, physical activity, and dietary intake after intervention, we will apply the Chi-square test while considering the app use as the dependent variable; the independent variables will be treatment adherence, physical activity, and dietary intake. For the MBG questionnaire, we will apply the Mann-Whitney test to compare the score between the groups before and after the intervention. The same test may be used to compare diastolic and systolic blood pressure measurements between the preintervention and postintervention groups. We will consider a 95% confidence interval (*P*<.05).

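### A compatible phone decides the group, but the three-variable propensity score names no baseline outcome and enters none of the stated tests, and the only definite blood pressure test does not compare groups

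*Protocol article*

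**What the plan says.** Under Study Population and Sample, group membership follows the eligibility criteria, with phone compatibility as the worked example. A patient who meets the common criteria but "does not have a mobile phone compatible with the app, then he or she will be allocated to the control group". For the other arm: "If the patient has a mobile phone compatible with the app, he or she will be allocated to the intervention group". Two further criteria, internet access on the phone and "Familiarity with the use of apps (intervention group)", apply to one arm only.

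The same section introduces a propensity score meant to reflect confounders or predictors of exposure, and says that for it "we will consider demographic variables of age, gender, and socioeconomic status". It does not say how the score will be used.

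Other baseline information is planned. Of the sociodemographic questionnaire, Evaluation and Assessment Frameworks says: "It includes questions on age, level of education, income, and experience in using a blood pressure meter". Under Preintervention Period: "We will collect the preintervention data from both groups from a sample characterization questionnaire and an MBG questionnaire". The abstract's Methods say that in both groups "we will assess and compare the evolution of blood pressure and treatment adherence before, during, and after the intervention".

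Statistical and Qualitative Analysis then assigns tests:
- **Blood pressure:** the paired t test. A Mann-Whitney comparison is mentioned as something that may be done.
- **Other quantitative variables, before and after:** paired t or Wilcoxon.
- **Adherence, physical activity and diet:** Chi-square, with app use as the dependent variable.
- **MBG score:** "For the MBG questionnaire, we will apply the Mann-Whitney test to compare the score between the groups before and after the intervention".
- **Further analyses:** a heterogeneity check on demographic and socioeconomic variables, an unspecified sensitivity analysis and, if feasible, a logistic regression with app use as the dependent variable.

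The propensity score is not mentioned again.

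**The concern.** The trial is openly nonrandomized, and that is not the complaint. The complaint is that assignment follows a patient characteristic plausibly linked to age, income, education and familiarity with technology, and that the stated analysis does not deal with it.

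There are three parts. First, the score names demographics only. The baseline values of the two outcomes the trial promises to compare, blood pressure and adherence, are not among them, although both are candidate confounders by the protocol's own description of what the score is for. Second, the score is attached to no test. Third, the definite blood pressure test asks whether pressure changed within patients. It cannot show that it changed more with the platform than with paper logbooks.

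At stake is the main conclusion. Any between-group difference reported from these tests could reflect who was eligible for the app rather than what the app did.

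**Working it through.** **The plan's own figure.** For 80% versus 40%, two-sided 5% (sidedness assumed) and 80% power:
- Without continuity correction: n = [1.96·√(2·0.6·0.4) + 0.842·√(0.8·0.2 + 0.4·0.6)]² / 0.4² = 22.3, so 23 per group.
- With continuity correction: 27.1, so 28 per group, as stated. 28 × 1.2 = 33.6, so 34, also as stated.

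The figure reproduces. It describes an unadjusted comparison of two proportions, with no allowance for a propensity score.

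**Where could the score enter?**

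| Stated analysis | Compares groups? | Carries the score or covariates? |
|---|---|---|
| Paired t, blood pressure | No | No |
| Paired t or Wilcoxon, other variables | No | No |
| Mann-Whitney, blood pressure (optional) | Apparently; wording unclear | No |
| Mann-Whitney, MBG | Yes | No |
| Chi-square, secondary outcomes | Yes | No |
| Heterogeneity check | Not a confounding adjustment | Demographic and socioeconomic variables |
| Logistic regression (if feasible) | Models app use, not blood pressure | Sociodemographics, with secondary outcomes as predictors |

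No row adjusts a blood pressure or MBG comparison for group differences.

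**Illustrative size.** The documents give no SD, correlation or baseline gap. Assume SD 15 mmHg, pre-post correlation 0.6, 28 per group, no platform effect, and a baseline gap of 5 or 8 mmHg that shrinks by the factor 0.6 by follow-up. For a bias b, the rejection probability is Φ(|b|/SE − 1.96) + Φ(−|b|/SE − 1.96).

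*Follow-up values, unadjusted.* SE = 15·√(2/28) = 4.01.
- Gap 5: b = 0.6 × 5 = 3.0 mmHg, rejection 0.116.
- Gap 8: b = 0.6 × 8 = 4.8 mmHg, rejection 0.224.

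*Change scores.* SD of change = 15·√(2 × 0.4) = 13.4; SE = 13.4·√(2/28) = 3.59.
- Gap 5: b = 3.0 − 5 = −2.0 mmHg, rejection 0.086.
- Gap 8: b = 4.8 − 8 = −3.2 mmHg, rejection 0.145.

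The sign reverses, so with the analysis left open even the direction of the bias is not fixed.

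*If the gap persisted in full,* the unadjusted follow-up comparison would reject in 24% (gap 5) or 51% (gap 8), and change scores would be unbiased. Baseline adjustment with slope 0.6 would then leave 5 − 3.0 = 2.0 or 8 − 4.8 = 3.2 mmHg. Adjustment removes the bias under the first assumption but not under this one.

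**Cost of weighting.** With 28 per group and 80% versus 40% (no continuity correction), power is 88% unweighted. Variance inflation of 1.2, 1.5 or 2.0 leaves 23.3, 18.7 or 14.0 effective patients per group and power of 82%, 72% or 59%.

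**The case against.** Several stronger readings are tempting, and the documents do not support them.

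- **That every smartphone owner enters the intervention group.** The criterion is a compatible Android phone, with internet access and app familiarity also required. An owner of an incompatible phone goes to control, and the text leaves open where the owner of a compatible phone goes if internet access or familiarity is lacking. Controls may therefore include smartphone owners.
- **That education is left out of the score.** Socioeconomic status is not defined, and education and income are both collected. Education is not named, but it may be included.
- **That the stated primary test has a 12% or 22% false-positive rate.** Those figures belong to an unadjusted follow-up comparison, which the protocol makes only optional. A baseline gap between groups does not act that way on a within-person paired t test. The figures also give no credit to the three-variable score.
- **That the design must become randomized.** The trial is declared and registered as nonrandomized. Randomizing eligible phone owners would be a different trial, not the correction of an error.

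The best general defence is that this is a condensed article. Whether a score is used by matching, weighting or as a covariate is often left to an analysis plan, and the text allows techniques to be modified. That excuses silence on technique. It does not excuse what is stated: a fixed list of three variables, and named unadjusted tests for the outcomes. An analysis plan would have to go beyond this text or contradict it, and a general permission to modify methods after seeing the data specifies no adjustment.

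**Conclusion.** The point holds in this form: allocation depends on a compatible phone and related criteria; the score names age, gender and socioeconomic status but neither baseline blood pressure nor baseline MBG; no stated test uses it; and the one definite blood pressure test makes no comparison between groups. This rests on the text and needs no assumption.

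The size is illustrative only. Under the assumptions above, the false-positive rate would be about 12% to 22% for unadjusted follow-up values and about 9% to 15% for change scores, with bias in the opposite direction, against a nominal 5%. The true imbalance is unknown.

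A limit remains after any repair. Phone eligibility determines the group, so analysis cannot separate its effect from that of the platform.

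**What to change.** 1. **Primary analysis.** Make it a between-group comparison of postintervention blood pressure, adjusted for its baseline value and for the propensity score, or directly for age, gender and socioeconomic status (with education if that is not already part of it). State how the score is used.
2. **MBG.** Analyse the postintervention score in the same way, with its own baseline value.
3. **Size of the model.** Keep the terms few, since about 28 evaluable patients per group will not support a long list. Report covariate balance and overlap.
4. **Baseline reading.** Name the baseline blood pressure measurement under Preintervention Period. That section lists only questionnaires, while the abstract implies a reading before the intervention.
5. **Conclusion.** Limit it to an association between being in the app group and blood pressure.

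**Cost.** Items 1 to 3 are analysis wording on data the protocol intends to hold. Item 4 is a clarification and item 5 is wording only. The statistical price is some precision if weighting or strong score adjustment is used: illustratively, power of about 72% at a variance inflation of 1.5, where 28 × 1.5 = 42 evaluable patients per group would be needed to keep 28 effective.

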To evaluate the findings’ heterogeneity (primary and secondary outcomes), we will apply a statistical technique to verify whether the differences observed in the results can be explained by chance. We will apply the Chi-square test with a significance level of *P*<.10. The magnitude of heterogeneity will be assessed by calculating the I^2^ value, which ranges from 0% to 100%. An I^2^ greater than 50% indicates substantial heterogeneity, and an I^2^ above 75% indicates considerable heterogeneity. For the evaluation of heterogeneity, we will consider the demographic and socioeconomic variables. In the presence of heterogeneity, we will investigate its causes through sensitivity analysis. In the sensitivity analysis, the form of data analysis varies, to identify the impact of this change on the results. All analysis techniques can be adjusted or modified, if required, by the characteristics of the collected data. If feasible, we also intend to analyze the results with logistic regression of preintervention and postintervention data. In this case, the dependent variable will consider the base category *whether* [user] *used the app*, related to independent, categorized, and continuous variables of interest such as sociodemographic variables and the expected secondary outcomes.

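### The propensity score, the only stated adjustment for confounding, lists age, gender and socioeconomic status and so leaves out every baseline clinical prognostic factor, including antihypertensive treatment

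*Protocol article*

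**What the plan says.** All references are to the Methods of the protocol article.

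- **Population** (Study Population and Sample): "The study population will include men and women under treatment for arterial hypertension". The criterion on care is "Current medical monitoring for the treatment of hypertension in the public health system". The listed criteria set no limit on the number of drugs and do not require a stable regimen.
- **Allocation** (same section): "If the patient has a mobile phone compatible with the app, he or she will be allocated to the intervention group". An otherwise eligible patient without such a phone goes to the control group.
- **Adjustment** (same section): the propensity score is meant to deal with confounders or predictors of exposure, and for it "we will consider demographic variables of age, gender, and socioeconomic status".
- **Blood pressure analysis** (Statistical and Qualitative Analysis): a paired t test is planned. After a sentence on comparing the adherence score between groups by Mann-Whitney, the article adds: "The same test may be used to compare diastolic and systolic blood pressure measurements between the preintervention and postintervention groups". No covariates are attached to either test.
- **Other analyses** (same section): for heterogeneity, "we will consider the demographic and socioeconomic variables". An optional logistic regression has app use as its dependent variable, and its independent variables are "variables of interest such as sociodemographic variables and the expected secondary outcomes".
- **Data collection** (Evaluation and Assessment Frameworks): the characterisation questionnaire names age, education, income and experience with a blood pressure meter, and then states: "The project researchers will provide the specifications".

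**The concern.** A propensity score can be relied on to balance only the variables in it. Two patients of the same age, gender and socioeconomic status may be on one drug or on three, with different starting pressures. Allocation by phone gives no protection against such a difference, and the eligibility criteria do not remove it.

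The list is introduced without any wording that would leave it open. The article therefore fixes the set and does not simply defer the detail. If treatment or starting pressure still differs between the groups after balancing on the three variables, that difference enters the between-group blood pressure comparison and is read as an effect of the platform. The direction cannot be known in advance: it could create an apparent benefit or hide a real one.

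**Working it through.** **1. Is the covariate repaired elsewhere?** No.
- The heterogeneity evaluation uses demographic and socioeconomic variables.
- The optional logistic regression models app use, so it yields no adjusted blood pressure effect, and its examples include no treatment variable.
- The general permission to modify analyses names no variable.

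**2. The article's group sizes.** Inputs: 80% versus 40%, 80% power, two-sided 5% (two-sided is assumed).
- Uncorrected: n = [1.96 × √(2 × 0.6 × 0.4) + 0.8416 × √(0.8 × 0.2 + 0.4 × 0.6)]² / 0.4² = (1.358 + 0.532)² / 0.16 = 22.3, so 23.
- With continuity correction: (22.3 / 4) × [1 + √(1 + 4 / (22.3 × 0.4))]² = 27.1, so 28, as stated.
- 28 × 1.2 = 33.6, so 34 per group and 68 in total. No figure is in dispute.

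**3. Illustrative bias in mmHg.** The article gives no regimen distribution, regimen effect or SD, so all of these are assumptions: a 10 to 30 point difference between groups in the share on a stronger regimen, a 5 to 10 mmHg effect of that regimen on level, an SD of 12 to 18 mmHg, pre/post correlation 0.6 and no platform effect.

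Spurious difference in postintervention values = share imbalance × level effect:
- 0.10 × 5 = 0.5 mmHg
- 0.20 × 7.5 = 1.5 mmHg
- 0.30 × 10 = 3.0 mmHg

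For pre/post change, multiply by the fraction of the level effect that does not cancel. Zero gives 0; one half gives 0.25, 0.75 and 1.5 mmHg.

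**4. False-positive rates.** Simulation: 28 per group, two-sided Mann-Whitney at 0.05, 20,000 trials per setting.

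| Spurious post-only difference | SD 12 | SD 18 |
|---|---|---|
| 0.5 mmHg | 4.8–5.3% | 4.9–5.1% |
| 1.5 mmHg | 6.9–7.0% | 5.6–5.8% |
| 3.0 mmHg | 13.1–13.4% | 8.4–8.6% |

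A second simulation gave about 5%, 5.6–6.8% and 8.6–14.3% in the three rows. At 34 per group and 3 mmHg the rates are 15.4% (SD 12) and 9.3–9.9% (SD 18).

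For change, full cancellation gives 4.5–4.9%. With half remaining, the largest case (1.5 mmHg) gives 7.5% (SD 12) and 6.1% (SD 18).

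If the three listed variables absorb half the imbalance, the mmHg figures halve. If they absorb all of it, the bias is zero.

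**5. The same question on the proportion scale.** Assume that baseline treatment shifts the chance of success by 20 to 40 points and differs between groups by 10 to 40 points. The bias is 0.2 × 0.1 = 2 points up to 0.4 × 0.4 = 16 points. With 34 per group and a 40% control rate, the chance of a false result favouring the app (nominal 2.5%) is about 4% to 26%. If the bias runs the other way, power falls from about 94% to between 91% and 51%. These inputs are wider than those in step 3, and the upper end is again an extreme corner.

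**6. Room for covariates.** Intervention participants per covariate, one term each: 34/3 = 11.3, 34/4 = 8.5, 34/5 = 6.8. At 28 per group: 28/3 = 9.3, 28/4 = 7.0, 28/5 = 5.6.

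**The case against.** The strongest reply has four parts.

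- **The score is not tied to the tests.** The article does not say how the score enters any analysis, and the named blood pressure tests are unadjusted. A further variable in the score would leave the rates in step 4 unchanged. This stands, and it shapes the fix: the score must also be applied. How a score is applied is commonly left to an analysis plan, so its absence here is not a separate fault.
- **Drug count is ambiguous.** More drugs may mark more severe disease and not lower pressure. This also stands. Baseline blood pressure should go in alongside it.
- **Residual imbalance is not shown.** Phone ownership plausibly follows age and socioeconomic status, which may carry most of the treatment difference. That is possible, and nothing in the article settles it either way.
- **The harmful case is optional.** The firm commitment is the paired test, the stated outcome is a reduction, and change largely cancels a level effect under a stable regimen. The Mann-Whitney comparison is only permitted, and its wording has to be read as between groups, by analogy with the adherence sentence before it. This limits the size of the concern. But a controlled trial sized on a between-group difference in proportions needs a between-group comparison, and that is where the omission counts.

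A reader might infer that regimen data will not be collected. The article does not support that: its instrument lists are not exhaustive, and the questionnaire's content is left to the researchers. Nor does it support adjusting away prescribing changes prompted by the dashboard, which are part of what the platform does.

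**Conclusion.** The point holds in a limited form. The stated covariate set contains no baseline clinical prognostic factor, and no other named analysis supplies one. The size of any resulting bias is unknown. Under the assumptions above it is negligible in many settings and probably small for pre/post change. It becomes material only when a large imbalance and a large regimen effect coincide in a post-only comparison.

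It would go too far to conclude that the trial's result will be confounded by treatment, or that its error rate is 13% or 14%: every clinical input behind those figures is assumed. This is a modest, inexpensive improvement to a choice the article has fixed too narrowly.

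**What to change.** 1. In Study Population and Sample, extend the propensity score to age, gender, socioeconomic status, baseline blood pressure and one baseline treatment summary, for example the number of antihypertensive drugs. Use a single summary and not one term per drug.
2. Make sure that summary is recorded in both groups at the existing preintervention meeting. Baseline blood pressure is already needed for the before-and-after comparison.
3. In Statistical and Qualitative Analysis, apply the score, by weighting or as a covariate, in the between-group blood pressure comparison, in place of the unadjusted test.
4. Keep the total effect of the platform as the main comparison. Adjust for baseline treatment only, not for later changes in regimen.

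The cost is a few minutes per participant and one or two more covariates in 68 participants. Intervention participants per covariate fall from 11.3 to 8.5 with one addition or 6.8 with both (from 9.3 to 7.0 or 5.6 if 28 per group complete). No visit is added and no treatment changes.
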